- Tolerance induction will attempted in the randomised group of children by blind daily intake of 1g wheat flour (100 mg gliadin, approximately 7-10 % of the gluten intake at age 1 year) during 8 weeks. Gluten is a common name used for some proteins (prolamins and glutenins) of wheat, barley, rye, and oats. Being gluten a naturally occurring component of food, it should be considered a food that is supplemented. Compliance will be assessed by 2 weekly visits or interviews.

The control intervention will take place by blind daily intake of 1g. lactose during 8 weeks.

Danone will provide the placebo (lactose, Pharmatose) and the intervention product (Glutival obtained from Cargill). Danone has outsourced the production of the identical sachets with the gluten intervention / placebo products to NIZO Food Research, Ede, the Netherlands.

NIZO will prepare and package the gluten intervention product as well as the placebo according to quality criteria adequate for infants aged 4-6 months..

Every intervention sachet will be filled 1.8 gr Pharmatose and 0.2 gr Glutival (gluten intervention product); the placebo sachets will be filled with 2 gr of Pharmatose.

NIZO will pay special attention to the microbiological assessment of the products and will make sure that the results will be in accordance with the standards of Danone. Also it will be analytically verified whether the blending of the materials has been adequate and resulted into a homogeneous mixture.

- Monitoring of early immune response to gluten in all the children: see Description of WP 6 “Immunological studies on early response to gluten introduction” and table 1.
- Nutritional assessment:

After the intervention, at the age of 6 months, all the families will be advised to gradually introduce gluten into the diet of their children. The parents will be advised to give the children 500 mg of gluten at the age of 7 months (10 g of ordinary biscuit ), 1000 mg at 8 months (10 g semolina and 10 g biscuits), 1500 mg at 9 months (20 g semolina, or pasta, and 10 g biscuits). After that, the children will consume "ad libitum" quantities of gluten-containing products. The use of breast-feeding and the quantities of gluten ingested will be assessed using

food frequency questionnaires (FFQ's) recently developed and validated by the Dutch partner.

Table 1. Time scheme of the assessments in the enrolled children

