### Description of work

- Assessment of the early immune response to gluten in approximately 1000 infants from high-risk families for CD from different European countries. The families will be invited to participate, among others, by the local Coeliac Disease Societies in collaboration with the Association of European Coeliac Disease Societies (AOECS). The CD Societies from the Netherlands (NCV)

([www.coeliakievereniging.nl](http://www.coeliakievereniging.nl)); Campania, Italy ([www.rcm.napoli.it/celiachia](http://www.rcm.napoli.it/celiachia)); Madrid (SCM) ([www.celiacosmadrid.org](http://www.celiacosmadrid.org)), Valencia (ACECOVA), Catalonia (SMAP) ([www.celiacscatalunya.org](http://www.celiacscatalunya.org)), Spain; Israel (CAI), Poland (PCS), Croatia, Hungary ([www.coeliac.hu](http://www.coeliac.hu)) and Germany ([www.dzg-online.de](http://www.dzg-online.de)) will collaborate in the study.

- The Societies will invite to participate their members with CD expecting a newborn (child or sibling) during the next 18 months. Informed consent to participate will be asked from the families by the local responsible physician.
- The children bearing HLA-DQ2 and/or DQ8 will be blindly randomised to either a group for "tolerance induction for gluten" or to a "control" group. At least 6 months of breast-feeding will be STRONGLY encouraged for all the children. At the age of 4 months tolerance induction will be attempted by the daily intake of 1g wheat flour (100 mg gliadin) during 8 weeks while continuing breast-feeding. No gluten will be given in these 8 weeks to control infants, but 1g. lactose as a placebo intervention. Danone will provide the placebo (lactose, Pharmatose) and the intervention product (Glutival obtained from Cargill). Danone has outsourced the production of the sachets with the gluten intervention / placebo products to NIZO Food Research, Ede, the Netherlands. NIZO will prepare and package the gluten intervention product as well as the placebo according to quality criteria adequate for infants aged 4-6 months. Every intervention sachet will be filled 1.8 gr Pharmatose and 0.2 gr Glutival (gluten intervention product); the placebo sachets will be filled with 2 gr of Pharmatose.  

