**Deliverables**

- D.6.1. Quantitative and qualitative analyses of the composition of the gluten used in the dietary intervention (m36);
- D.6.2 Collection of breast-milk samples (m 36)
- D.6.3 Quantitative and qualitative analyses of the composition of gluten present in breast-milk of the mothers participating in the study (m44)
- D.6.4 Analysis of the repertoire of gluten specific T cells in children developing CD during the intervention family study (m 45)
- D.6.5 Analysis of the immunological impact of the dietary intervention on the regulatory T cell compartment (m45).
- D.6.6 Analysis of the spectrum of mucosal immune abnormalities in infants “at-risk” for CD in relation to their genetic background (m45).

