**Executive summary:**

**Problem I: Gluten will be given to the infants at the age of 4-6 months, which is against the current recommendations of WHO and ESPGHAN.**

The project is - in principal – strongly backing the general principle of breast feeding, which is the only generally accepted prevention strategy with respect to CD. This leading principle is clearly in line with current recommendations.

The current WHO and ESPGHAN recommendations refer to the general population, but not to the high risk group predisposed to CD as within the family study of this project. For this sub-population, there are no guidelines at all.

The strong recommendation of ESPGHAN not to feed gluten before month 4 will strictly be followed. The current advice for the age between months 4 and 5 (and later) is less strict in the current recommendations.

Gluten is given only in the lowest possible amount expected to have an effect on the immune system (max. 100 mg), which is much lower (aprox. 3%) and not comparable to the amount of gluten introduced as complementary food after weaning (grams).

There are several studies on epidemiology and basic immunological principles supporting the “window of opportunity concept”. Scientific studies by the Swedish partner of PREVENTCD exploring in detail the "CD epidemic" in Sweden, strongly support introduction of gluten during the 4th to the 5th month of age not to increase the risk for CD, and possibly also to decrease the risk. Notably, the CD epidemic started in 1983 when gluten introduction was postponed from month 4 to 6 by changed national recommendations to parents, and also the baby food producers taking out existing gluten from products aimed for this age-group. Moreover, the epidemic subsided when gluten introduction in 1996 was once again “allowed” from 4 months of age.

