CD is mainly a genetically-based immunologically-mediated disorder, whose major feature concerns a destructive immunologic/inflammatory process of the upper small intestine in genetically predisposed individuals who consume gluten. According to the immunological principles regarding treatment protocols whereby tolerance to an offending antigen can be induced by very small quantities of this same antigen, PREVENTCD considers that these principles can be employed in order to produce a benefit on the health of the coeliac-prone infant: that is, to render him/her tolerant to gluten by administration of very small quantities of this antigen, to avert – or at least minimize – the manifestation of frank CD. The dose of 100 mg, which is less than 3% of the amount of gluten introduced in the diet at weaning time (Hopman, 2007) is the lowest that can be expected to have an effect on the immune system (Catassi 1993), which is a requirement for immunomodulatory effects and for the possible induction of tolerance to avoid the development of CD. PREVENTCD does not propose to advance the current introduction of gluten into the diet of the children prone to CD: that is the administration of (relatively) large quantities of gluten at once, but to administer 100mg gluten per day, an amount not comparable to those usually given at the weaning time. Therefore, it should not be considered “gluten introduction”, but rather a gluten tolerance-inducing procedure. Notably, the current dietary advice with respect to gluten introduction to infants is not evidence-based. The only international guideline available is the one mentioned above by ESPGHAN, and the studies behind this recommendation do not at all fulfil today’s requirements for valid scientific evidence. This is important to consider because, since this recommendation was launched, the incidence of CD in Europe has not decreased, but increased (Auricchio

1992; Catassi 2001, [name] 2000, Steens 2005) suggesting that the current dietary advice does not necessarily represent a benefit for the participating children.

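### The daily study product is described in ways that cannot all be true: 1 g flour or a 2 g sachet, 1 g or 2 g of placebo, and 100 mg of gliadin or 100 mg of gluten

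*Protocol*

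**What the plan says.** **Product.** In Protocol 7.6, Work Package 3, the Introduction gives the active intervention as "blind daily intake of 1g wheat flour (100 mg gliadin, approximately 7-10 % of the gluten intake at age 1 year) during 8 weeks". The Description of work repeats it: "tolerance induction will be attempted by the daily intake of 1g wheat flour (100 mg gliadin) during 8 weeks". Both places then describe the manufactured product differently: "Every intervention sachet will be filled 1.8 gr Pharmatose and 0.2 gr Glutival (gluten intervention product". The description of partner 8 in Appendix A and section A.2 (Sub-contracting) give the same sachet contents.

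**Control.** "The control intervention will take place by blind daily intake of 1g. lactose during 8 weeks". The manufacturing text that follows fills each placebo sachet with 2 g of Pharmatose, which the protocol identifies as lactose.

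**Active content.** Work Package 3 counts 100 mg of gliadin. Section 9.3, Problem I of the executive summary, counts gluten: "Gluten is given only in the lowest possible amount expected to have an effect on the immune system (max. 100 mg". The longer ethics discussion that follows also speaks of 100 mg of gluten per day and calls the dose "less than 3% of the amount of gluten introduced in the diet at weaning time".

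**Definition.** The Work Package 3 Introduction defines gluten as covering both prolamins and glutenins.

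**Checks on the product.** The manufacturing checks listed are microbiology and homogeneous blending. Work Package 6 plans a composition report: "D.6.1. Quantitative and qualitative analyses of the composition of the gluten used in the dietary intervention (m36".

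**The concern.** The family trial tests one small daily amount against placebo, so that amount is part of its conclusion and of any feeding guideline drawn from it. The amount also carries weight in the ethics argument. Section 9.3 meets the objection that exposure at 4 to 6 months departs from current advice by saying the dose is the lowest likely to affect the immune system, and it goes on to class the intervention as minimal risk. That argument is made for 100 mg of gluten. The section that specifies the intervention says 100 mg of gliadin, and gliadin is only one component of gluten. If Work Package 3 describes what infants receive, the ethics section understates the gluten they are given. If the ethics section is accurate, Work Package 3 overstates the gliadin. The two descriptions of the powder do not settle which applies.

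**Working it through.** **Inputs from the protocol**
- Active, description A: 1 g wheat flour per day holding 100 mg gliadin (7.6, Work Package 3).
- Active, description B: sachet of 1.8 g Pharmatose + 0.2 g Glutival (Work Package 3, partner 8, A.2).
- Control: 1 g lactose per day, or a sachet of 2 g Pharmatose (Work Package 3).
- Ethics figure: 100 mg gluten per day (9.3).

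**Not given in the protocol, so assumed over a range**
- Gliadin share of gluten, *f*: 40 to 60%.
- Gluten content of Glutival, *p*: 70 to 100%.
- Sachets per day, *k*: 1, or one half.

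**Step 1. The two active descriptions.** Sachet mass is 1.8 + 0.2 = 2.0 g, which matches the 2 g placebo sachet but not the 1 g of flour or the 1 g of lactose. The stated 100 mg of gliadin is 100/1000 = 10% of 1 g flour, but 100/200 = 50% of 0.2 g Glutival. A lactose and Glutival blend is in any case not flour.

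**Step 2. Gliadin against gluten.** Gluten = gliadin / *f*. Work Package 6 plans to measure fragments from both gliadin and glutenin in the intervention product, so the plan itself expects *f* to be below 1. Then 100 mg of gliadin always means more than 100 mg of gluten. Over the assumed range:
- *f* = 0.6: 100/0.6 = 167 mg gluten
- *f* = 0.5: 100/0.5 = 200 mg
- *f* = 0.4: 100/0.4 = 250 mg

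This is 1.7 to 2.5 times the ethics figure. The direction needs no assumption; only the size does.

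**Step 3. Can any number of sachets reconcile the set?** Gluten = 200 mg × *k* × *p*; gliadin = gluten × *f*.

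| Sachets per day | Powder | Gluten | Gliadin | Fits 1 g control? | Can fit 100 mg gliadin? | Within 100 mg gluten? |
|---|---|---|---|---|---|---|
| 1 | 2 g | 140–200 mg | 56–120 mg | No | Yes, at the upper end | No |
| ½ (stated nowhere) | 1 g | 70–100 mg | 28–60 mg | Yes | No | Yes |

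The pair 0.2 g Glutival and 100 mg gliadin can agree, for instance at *p* = 1.0 and *f* = 0.5. The full set cannot: by step 2, no dose delivers 100 mg of gliadin and at most 100 mg of gluten.

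**Step 4. The relative-dose percentages.** Taken at face value, 100 mg as 7 to 10% of intake at age 1 implies 100/0.10 = 1000 to 100/0.07 = 1429 mg of gluten a day. The same 100 mg as 3% of the weaning amount implies 100/0.03 = 3333 mg. The first calculation, however, sets a gliadin dose against a gluten intake. With the dose converted to 167 to 250 mg of gluten, the age-1 intake becomes 167/0.10 = about 1.7 g to 250/0.07 = about 3.6 g, a range that contains 3.3 g at its upper end. The gap between the two percentages may therefore be the step 2 discrepancy appearing again, and it is not counted separately.

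**Step 5. Timing of the composition report.** D6.1 is due at month 36, the month in which D3.6 has 1000 newborns enrolled. D3.5 has 700 at month 24, so accrual is 300/12 = 25 a month. Treating enrolment as birth and accrual as even (assumptions), those born by month 30 have completed the 8 weeks by month 36: 700 + 6 × 25 = 850 of 1000.

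**The case against.** The strongest defence is that the sachet contents are identical in four places, that 1 g flour can be read as a food-equivalent description left over from planning, and that 0.2 g Glutival can supply 100 mg of gliadin. On that view the product is defined and only loose wording remains. Part of this stands: the sachet is described consistently, and it would be wrong to infer that the product cannot be identified at all. But the number of sachets per day and the gluten content of Glutival are missing, and this reading contradicts both the 1 g control and the 100 mg of gluten in the ethics section.

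Several stronger readings are tempting, and the documents do not support them.
- **A further conflict with the trial's own feeding advice.** The schedule says "The parents will be advised to give the children 500 mg of gluten at the age of 7 months", and 100/500 is 20%, not 3%. But the 3% refers to the amount usually introduced at weaning, and the trial's schedule is deliberately gradual. The comparators differ.
- **7–10% against 3% as a separate error.** These refer to different ages, and the implied intakes can overlap once gliadin is converted to gluten (step 4).
- **Almost all infants dosed with an untested product.** Month 36 is when a report is due, not when the first assay is run. The work described concerns T-cell-stimulatory fragments and T-cell reactivity, not release of the product by dose. On the stated enrolment targets, about 15% of infants would not yet have finished by then.
- **An approved maximum breached.** The 100 mg ceiling is the consortium's own argument. Section 9.3 leaves approval of the family study to local committees, whose decisions are not in the document.
- **A conflict with the consent text.** The consent pages are not available, so nothing can be said about them.

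**Conclusion.** The point holds as an internal contradiction in current protocol text, and it should be corrected. Three pairs of statements conflict: flour against a lactose and Glutival sachet, 1 g against 2 g of control product (a two-fold difference), and 100 mg of gliadin against 100 mg of gluten. The third follows from the protocol's own definition of gluten. Its size, 167 to 250 mg of gluten or 1.7 to 2.5 times the ethics figure, rests on the assumption that gliadin is 40 to 60% of gluten. That no reading satisfies every figure does not depend on that range.

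It matters because the daily amount is what the trial's conclusion will be about, and because the lowest-amount and minimal-risk argument relies on the lower reading. Sample size, randomisation and endpoint are not affected.

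The timing of D6.1 is a note only: no stated check requires the gluten or gliadin content of the product to be known before use. The passages must be reconciled; which dose is right is not a matter for this review.

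**What to change.** 1. Reconcile Work Package 3 (Introduction and Description of work), section 9.3 (executive summary and detailed discussion), the partner 8 description and section A.2 to one statement for each arm: the product, the sachets per day, and the mg of gluten and of gliadin per day. State the gluten content of Glutival.
2. Restate the 7–10% and 3% comparisons on that single basis, each with its comparator named.
3. Re-read the lowest-amount and minimal-risk argument in section 9.3 against the reconciled figure.
4. As a note, because start-up recruitment is already described in the past tense: confirm the gluten and gliadin content of each remaining batch before it is used, in addition to the microbiology and blending checks.

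Items 1 to 3 cost protocol wording only. Item 4 adds a content check per batch; methods for analysing the gluten preparation are already planned in Work Package 6.

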### Objectives

Assessment of the possibilities to achieve primary prevention for CD in genetically predisposed children by early dietary intervention consisting of introduction of small quantities of gluten during the period of breast-feeding

### Description of work

- Assessment of the early immune response to gluten in approximately 1000 infants from high-risk families for CD from different European countries. The families will be invited to participate, among others, by the local Coeliac Disease Societies in collaboration with the Association of European Coeliac Disease Societies (AOECS). The CD Societies from the Netherlands (NCV)

([www.coeliakievereniging.nl](http://www.coeliakievereniging.nl)); Campania, Italy ([www.rcm.napoli.it/celiachia](http://www.rcm.napoli.it/celiachia)); Madrid (SCM) ([www.celiacosmadrid.org](http://www.celiacosmadrid.org)), Valencia (ACECOVA), Catalonia (SMAP) ([www.celiacscatalunya.org](http://www.celiacscatalunya.org)), Spain; Israel (CAI), Poland (PCS), Croatia, Hungary ([www.coeliac.hu](http://www.coeliac.hu)) and Germany ([www.dzg-online.de](http://www.dzg-online.de)) will collaborate in the study.

- The Societies will invite to participate their members with CD expecting a newborn (child or sibling) during the next 18 months. Informed consent to participate will be asked from the families by the local responsible physician.
- The children bearing HLA-DQ2 and/or DQ8 will be blindly randomised to either a group for "tolerance induction for gluten" or to a "control" group. At least 6 months of breast-feeding will be STRONGLY encouraged for all the children. At the age of 4 months tolerance induction will be attempted by the daily intake of 1g wheat flour (100 mg gliadin) during 8 weeks while continuing breast-feeding. No gluten will be given in these 8 weeks to control infants, but 1g. lactose as a placebo intervention. Danone will provide the placebo (lactose, Pharmatose) and the intervention product (Glutival obtained from Cargill). Danone has outsourced the production of the sachets with the gluten intervention / placebo products to NIZO Food Research, Ede, the Netherlands. NIZO will prepare and package the gluten intervention product as well as the placebo according to quality criteria adequate for infants aged 4-6 months. Every intervention sachet will be filled 1.8 gr Pharmatose and 0.2 gr Glutival (gluten intervention product); the placebo sachets will be filled with 2 gr of Pharmatose.  
NIZO will pay special attention to the microbiological assessment of the products and will make sure that the results will be in accordance with the standards of Danone. Also it will be analytically verified whether the blending of the materials has been adequate and resulted into a homogeneous mixture. Compliance will be assessed by visit or interview.
- After the 8 weeks intervention period, all the families will be advised to gradually introduce gluten into the diet of their children, and to increase it gradually till the age of 12 months, for which simple recommendations will be provided to the parents.
- The infants will be strictly followed up (Table 1). Blood (5 ml) is sufficient to allow for the screening of CD-specific antibodies, phenotypic characterization of 20 markers indicating lymphocyte activation and regulatory T cell induction, and monitoring for the occurrence of gluten-specific T cell responses typical for CD. At age 3 years 10 ml blood will be obtained to test for additional (auto)immune phenomena related to the development of CD.
- Children with positive antibodies strongly indicating CD or with clinical suspicion of CD will be offered a small bowel biopsy for the definitive diagnosis a reduction of 50% of CD among the intervention group at the age of 3 will be considered as an effective prevention.

### **Deliverables**

- D.3.1 European databank on the complex interaction between early gluten intake and breast-feeding in children from high-risk families for CD, their early immune response to gluten and to other related auto-antigens and their genetic background (m 44)
- D.3.2 Assessment of the possibilities to achieve primary prevention for CD in genetically predisposed children by early dietary history intervention (m 46)
- D.3.3 New European guidelines for early nutrition, concerning gluten introduction and breast-feeding (m 48)
- D.3.4 350 newborns enrolled (m12)
- D.3.5 700 newborns enrolled (m 24)
- D.3.6 1000 newborns enrolled (m 36)

**Milestones and expected result**

M3. First year analysis (m 12)

M4. Mid-term analysis (m 24)

M5. Presentation of the results during the final meeting (m 60)

Development of a common European databank on the complex interaction between early gluten intake by European young children with a high-risk for CD, their early immune response to this food antigen and their genetic background

## **Work Package (WP) 4: Population based study exploring birth cohorts with different early dietary history**

### **Introduction**

We will take advantage of the “experiment” in the Swedish population with extensive changes in infant feeding practices within a few years, which resulted in a unique epidemic of symptomatic CD in children below 2 years of age. The incidence rate of symptomatic CD increased four-fold to levels higher than ever previously reported, and after a ten-year period on this high level, suddenly returned back to the previous level. A representative sample of 16.000 Swedish children aged 12 years, 8.000 born during the peak of the epidemic (1993) and 8.000 born after the epidemic (1997), will participate in the study. This study is based on a long-standing collaboration with paediatric units in different parts of Sweden, and also a well-developed collaboration with the school health services.

- Design: prospective population based intervention study with a long-term follow-up
- Study base: the study on the 8.000 children from the epidemic will be done before the project, but the results will be used to be compared with the data from the cohort from the post-epidemic period.
- Invitation to participate: requirement for inclusion is an informed consent from the child and its parents.
- Symptomatic CD cases diagnosed before the age of 12-years will be identified through the National Register of CD in Swedish children.
- Screening for CD: all children will be invited for a blood sample during the school-year 2009-2010 for determination of tissue transglutaminase antibodies type IgA (AtTG), and those with s-IgA-deficiency also for AtTG type IgG. When CD is suspected the child is referred for a diagnostic small bowel biopsy. Biopsies will only be performed when medically indicated, that is: only in these children with CD antibodies in their serum that indicate gluten sensitivity and are highly suspect for active CD, and NOT just for purpose of the study. Such children would undergo a biopsy also in non-study circumstances.

- Double the numbers of screening-detected cases in the epidemic cohort are expected compared to the cases in the post-epidemic cohort.
- HLA and non-HLA genetic characteristics and autoimmune serological markers will be assessed in all the children with CD (symptomatic and screening-detected) and in 5 population based controls per case (n=1800).
- Early dietary history: The parents will be asked to fill in a questionnaire about the child's history with respect to breast-feeding and early gluten exposure.
- Statistical power analysis: A sample size of 5.000 participants from each cohort is necessary to determine an expected difference in prevalence of CD between the cohorts of the epidemic (1993) and post-epidemic (1997) periods. However, to get enough CD cases also for sub-studies the number of participant invited children will be 8.000 in each cohort.

|                                |                |   |     |   |                               |   |   |   |   |    |    |    |         |    |    |    |    |  |
|--------------------------------|----------------|---|-----|---|-------------------------------|---|---|---|---|----|----|----|---------|----|----|----|----|--|
| Work package no.               | 4              |   |     |   | Start date or starting event: |   |   |   |   |    |    |    | Month 1 |    |    |    |    |  |
| Activity Type                  | RTD/Innovation |   |     |   |                               |   |   |   |   |    |    |    |         |    |    |    |    |  |
| Participant id                 | 1              | 2 | 3   | 4 | 5                             | 6 | 7 | 8 | 9 | 10 | 11 | 12 | 13      | 14 | 15 | 16 | 17 |  |
| Person-months per participant: | 0              | 0 | 116 | 0 | 0                             | 0 | 0 | 0 | 0 | 7  | 19 | 0  | 0       | 0  | 0  | 0  | 0  |  |

